**Figure 4 fig4:**
[figure not shown]
Biomechanical model and anatomical placement of motion capture markers. **(A)** Dynamometric platform used in the biomechanical gait assessment. **(B)** Instrumentation of Inertial Sensor Units measure, which will be attached by elastic straps provided by the manufacturer. Each sensor must be placed at the following zones: **(B.1)** Lumbar, located just below the spinosa of the lumbar vertebra 5. **(B.2)** Thighs, located at the lower limit of the upper third of the thigh, on its lateral surface. It is considered as the total measurement of the thigh from the greater trochanter to the interarticular line. **(B.3)** Legs, placed at the midpoint of the leg measured from the interarticular line to the medial malleolus. The sensor is positioned just medial to the tibial border. **(B.4)** Feet, positioned on the dorsum of the foot, four centimeters from the intersection of the inter-malleolar line, above a line projected toward the fourth toe.

The study’s primary outcome is Gait speed at the post-training time (primary time point), defined as the distance traveled by the body per unit of time (m/s). The Gait speed is an objective variable, easy to measure with or without instrumental equipment, and considered a relevant indicator of functional and health status (54, 55). In addition, the secondary outcomes of this trial are the Maximum gait speed (m/s) (56) and the Gait speed variability, calculated through the coefficient of variation ([standard deviation/mean] × 100) (57), which indicates how stable or repeatable the participants are when walking. These variables could be more sensible to gait impairments (58) and changes after treatment (57). On the other hand, the tertiary outcomes are those from the spatiotemporal, kinematics, and kinetics gait analysis, in addition to the scores of the scales and questionnaires proposed in Table 1.

#### Sample size and recruitment

2.2.4

Sample size calculation has been done with the G*Power software (Universität Kiel, Germany, Version 3.1) (59), based on the expected differences in gait performance between experimental and control groups. Due to the absence of statistical differences between groups in the previous works that compare gait physiotherapy with and without MI, the estimation was settled with a small expected size effect of *F* = 0.15 (60). A power of 80% and a type I statistical error of 5% were considered in a mixed factorial design (2 groups and 3 times assessments), which resulted in 74 participants as the total sample size. Considering 20% of drop-outs, the recruitment will be 44 people per group. For the participant’s recruitment, the research coordinator of the study will establish communication with local health centers to provide information and contact details about the GAITimagery study. The centers will be asked to distribute this information among potential participants through brochures, after which those interested in participating will have to communicate their intention by telephone to the coordinator research. After this, an appointment to evaluate the participation criteria and the severity of the disease will be given to the people who have established communication with the study. The recruitment process will remain open until the necessary number of people is met according to the sample size calculation, as long as it does not exceed 2 years. If this time ends, the preliminary results will be reported, informing the power of the study fulfilled with the sample obtained.

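### The 80% power behind N = 74 belongs to a Group x Time interaction at f = 0.15, not to a small between-group difference in gait speed at t1, the primary endpoint

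*Protocol article*

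**What the plan says.** Section 2.2.4 (Sample size and recruitment) of the protocol article describes the calculation as "based on the expected differences in gait performance between experimental and control groups". Because earlier trials with and without motor imagery found no group differences, "the estimation was settled with a small expected size effect of *F* = 0.15". The section continues: "A power of 80% and a type I statistical error of 5% were considered in a mixed factorial design", with two groups and three assessments, and the result is 74 in total, with 44 per group to be recruited after allowing for drop-out. The section does not say which F test was powered, which correlation between visits was used, or what difference in m/s or SD the effect size stands for.

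Section 2.2.3 fixes the endpoint at one visit: the "primary outcome is Gait speed at the post-training time (primary time point"). Section 2.4 plans a two-factor mixed MANOVA (Group by Time, three times) with Bonferroni post-hoc comparisons. No other power statement covers the primary endpoint.

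**The concern.** The wording of section 2.2.4 invites the reader to attach the 80% to a small difference between arms. In a 2 x 3 mixed design, however, G*Power offers several tests, and one value of f means a different thing in each. If 74 comes from the interaction, f measures how much the group difference varies over the three visits, which is neither the group difference at t1 nor obviously small on that scale.

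This affects how the result is used. The abstract says the findings will inform whether session time should go to imagery, depending on the effect size. If the protocol is taken to have 80% power for a small benefit, a non-significant result will be read as evidence against a small benefit. Section 2.2.4 also promises to report the power achieved if recruitment falls short, and that figure is undefined until the powered contrast is named.

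**Working it through.** **Inputs from the protocol article.** f = 0.15, power 80%, alpha 0.05, k = 2 groups, m = 3 times, G*Power 3.1, N = 74, 1:1 allocation (37 per arm). **Assumed, because not given:** correlation between visits rho = 0.5 and sphericity (epsilon = 1).

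**1. Reproduce 74.** For the within-between interaction, lambda = f² N m / (1 − rho), df1 = (k − 1)(m − 1) = 2 and df2 = (N − k)(m − 1).
- N = 74: lambda = 0.0225 × 74 × 3 / 0.5 = 9.99, df = 2 and 144, power 0.806.
- N = 72: lambda = 9.72, df = 2 and 140, power 0.795.

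So 74 is the smallest even N that reaches 80%. The Time main effect with two groups has the same lambda and df and also gives 74, but it says nothing about motor imagery.

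**2. The between-group test at the same f.** lambda = f² N m / (1 + (m − 1) rho), df = 1 and N − 2. At N = 236, lambda = 0.0225 × 236 × 3 / 2 = 7.97 and power is just over 0.80; N = 234 falls just short. So 74 is not a between-group calculation under these assumptions.

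**3. What f = 0.15 means in the interaction.** Let d_t be the group difference at visit t in within-cell SD. Then f² = (1/4) × mean over t of (d_t − mean d)². With no baseline difference:

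| Group difference at t0, t1, t2 | f² | t1 difference at f = 0.15 |
|---|---|---|
| 0, d, d (kept) or 0, d, 0 (lost) | d²/18 | 0.15 × √18 = 0.64 SD |
| 0, d, 0.5d (half kept) | d²/24 | 0.15 × √24 = 0.73 SD |
| 0, d, 0.75d or 0, d, 0.25d | – | 0.71 SD |
| 0, d, 1.5d (grows by half) | – | 0.48 SD (0.72 at t2) |
| 0, d, 2d (doubles) | d²/6 | 0.15 × √6 = 0.37 SD (0.73 at t2) |
| 0, d, −d (reverses) | d²/6 | 0.37 SD |

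**4. Power for the t1 contrast, 37 per arm.** Two-sample t test with noncentrality d × √(37/2) and 72 df.
- d = 0.30, the two-group equivalent of f = 0.15 at a single visit (d = 2f): noncentrality 0.30 × 4.301 = 1.29, power 25%. With baseline ANCOVA at rho = 0.5 it is 31%.
- d = 0.64: power about 77%.
- Difference detectable with 80% power: 0.66 SD unadjusted at alpha 0.05; 0.77 SD at alpha 0.05/3 (an assumed three-comparison Bonferroni correction); 0.66 × √(1 − 0.5²) = 0.57 SD with ANCOVA at rho = 0.5.

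**5. Sensitivity to the unstated correlation.** At N = 74 and f = 0.15, interaction power is about 65% at rho = 0.3 and 96% at rho = 0.7. The sustained difference (0, d, d) detectable with 80% interaction power is 0.75 SD at rho = 0.3, 0.63 at 0.5, 0.49 at 0.7 and 0.40 at 0.8.

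**The case against.** The strongest reply is that nothing has been miscalculated. The section names a two-group, three-time design, 74 is right for its f, and "small" may be meant on the scale of f itself, resting on a cited source that is not at hand. The text never says in so many words that the trial has 80% power for a small difference in gait speed at t1. All of this stands. The fault is an effect label and a power statement that do not fit the primary endpoint.

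Stronger readings that a reader might infer, and that the document does not support:
- *That f = 0.15 implies at least 0.64 SD at t1.* This is not a lower bound at t1: an effect that doubles by t2 gives 0.37 SD. Section 2.2.2, though, describes gait benefits as emerging quickly and lasting, which is the kept profile and gives 0.64 SD.
- *That 74 can only be the interaction.* The test is inferred from the reproduced N. The Time main effect gives the same number, and rho = 0.5 is an inference too.
- *That only a medium-to-large benefit could be detected or excluded.* At rho = 0.8 a sustained 0.40 SD would be detectable through the interaction. What a null result excludes depends on its confidence interval, not on planned power.
- *That the protocol repeats the error it criticises in its Introduction.* The Introduction objects to sizing on within-group change. An interaction contrasts change between groups.

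One could also say that the correlation and sphericity settings are detail an article leaves to the full protocol. Their absence is not the point here; they are needed only because the stated description does not match the number produced.

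**Conclusion.** The point holds as a mismatch between the powered effect and the primary endpoint, made worse by a misleading label. The 80% applies to an interaction-type test at f = 0.15. It does not apply to a small between-group difference in gait speed at t1. For an effect that has appeared by t1 and does not grow or reverse afterwards, the implied t1 difference is 0.64 to 0.73 SD. A t1 t test with 74 completers has about 25% power at 0.30 SD and reaches 80% at about 0.66 SD.

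These figures assume no baseline difference. The attribution to the interaction also assumes rho = 0.5 and sphericity, neither of which the article states. The unadjusted t-test figures do not depend on rho.

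**What to change.** In section 2.2.4:
- Say that 74 powers the Group x Time interaction, and give the correlation and sphericity assumptions used. If a different test was used, name it.
- Stop describing the implied between-group difference as small.
- State the difference in gait speed at t1 detectable with 80% power under the analysis actually planned for t1, in SD and in m/s with an assumed SD. For 74 completers this is about 0.66 SD for an unadjusted comparison at alpha 0.05, and larger if Bonferroni-corrected (0.77 SD for three comparisons). About 0.57 SD, at correlation 0.5, may be quoted only if section 2.4 also adopts a baseline-adjusted ANCOVA as the t1 analysis; the mixed MANOVA now planned does not include one.

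The conversion to m/s needs an SD that the document does not give, so the sponsor must supply and justify one. Enrolment does not change. The cost is a reworded paragraph and a less favourable stated detectable effect.

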A two-factor mixed Multivariate Analysis of Variance (MANOVA) will be conducted to analyze the factors effects on the outcomes registered at t0, t1, and t2. The within-subject factor is *Time* with three categories (Baseline, Postintervention and Follow-up). The between-subject factor is *Group* with two categories (GiG and GaG). When significant effects are found, Bonferroni will be used for post-hoc comparisons. Differences shall be declared statistically significant if *p* < 0.05. Before the referred statistical analysis above, the following assumptions will be checked: (1) Normality: the distributions of the residuals will be tested using the Shapiro–wilk test; (2) Sphericity: the homogeneity between variances of the differences between pairs of measures will be checked with the Mauchly sphericity test; (3) Homoscedasticity: homogeneity of variances will be evaluated using the Levene test; (4) Equality of covariance matrices: the equality of variance–covariance matrices across the cells formed by the between-subjects effects will be tested with the Box’s *M* test; (5) Absence of multicollinearity, the correlation level between dependent variables will be observed with the Pearson correlation test. If any of these assumptions are not met, the necessary statistical corrections will be used (61).

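### The 80% power printed for N=74 belongs to a single-outcome repeated-measures interaction and does not apply to the multi-outcome MANOVA that is the only test written

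*Protocol article*

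**What the plan says.** Section 2.2.4 names the software ("Sample size calculation has been done with the G*Power software") and a "small expected size effect of *F* = 0.15". Power (80%) and type I error (5%), it says, "were considered in a mixed factorial design (2 groups and 3 times assessments), which resulted in 74 participants as the total sample size". It gives no number of dependent variables, no correlation between visits and no sphericity assumption. Recruitment is then raised to 44 per group for drop-out.

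Section 2.2.3 names one primary outcome, gait speed at t1, two secondary outcomes (maximum gait speed and gait speed variability), and makes the rest of Table 1 tertiary.

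Section 2.4 writes the comparative test: "A two-factor mixed Multivariate Analysis of Variance (MANOVA) will be conducted to analyze the factors effects on the outcomes registered at t0, t1, and t2". Time (three levels) and Group (two levels) are the factors. Bonferroni comparisons follow when effects are significant. One of the listed assumption checks is "Absence of multicollinearity, the correlation level between dependent variables will be observed with the Pearson correlation test". Another is Mauchly's test of sphericity. No separate test of gait speed at t1 is named, and the outcomes that enter one model are not listed.

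**The concern.** A sample size and its power belong to a particular test. Here the sizing describes a design with two groups and three visits, and nothing in it refers to more than one outcome. The analysis describes a multivariate test, and a check of correlation between dependent variables has meaning only when a model holds more than one. Each outcome added to such a test adds two hypothesis degrees of freedom for Group x Time and uses up two of the error degrees of freedom, so the number of outcomes changes the power directly.

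Two things are at stake. First, the 80% is the only power statement in the article, and the only written comparison is not the one it describes. The Introduction criticises earlier trials for samples that may have been too small, so readers will take the figure seriously. Second, section 2.2.4 promises to report the power achieved if recruitment stops at two years. That report needs a power calculation that matches the test.

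**Working it through.** **Inputs.** From section 2.2.4: f = 0.15, alpha = 0.05, power 80%, k = 2 groups, m = 3 visits, N = 74. Assumed because not printed: correlation between visits rho = 0.5 and sphericity (epsilon = 1). The number of outcomes p is not fixed in the text. By count, Table 1 has 24 rows measured at t0-t2 (6 clinical, 18 biomechanical). This becomes 26 when the two rows holding two instruments each are split, and about 30 when the other combined rows are split too. The correlation r between outcomes is not given either, so a range is used.

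**Step 1: reproduce the printed figure.** For the Group x Time interaction on one outcome:

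- lambda = f² x N x m / (1 - rho) = 0.0225 x 74 x 3 / 0.5 = 9.99
- df1 = (k-1)(m-1) = 2; df2 = (N-k)(m-1) = 72 x 2 = 144
- Power = 80.6%. At N = 73 it is 80.1% and at N = 72 it is 79.5%, so the first size with equal arms is 74.

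The printed figure is reproduced. With two groups the Time main effect has the same formula and also gives 74, but section 2.2.4 bases the calculation on differences between the groups, so the interaction is the relevant test. Other readings do not give 74: the between-group main effect at rho = 0.5 needs 236, and the multivariate repeated-measures option with f(V) = 0.15 needs 432. The unprinted rho matters: the interaction needs 146 at rho = 0, 102 at rho = 0.3 and 46 at rho = 0.7.

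**Step 2: power of a Group x Time MANOVA on p outcomes.** With two groups the doubly multivariate test is an exact F:

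- df1 = 2p; df2 = N - 1 - 2p
- lambda = 9.99 x Q, where Q = d'R⁻¹d, d marks the responding outcomes (each at the sized effect), and R has a common correlation r
- For s responding outcomes out of p: Q = [s - r s² / (1 + (p-1)r)] / (1 - r)

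| p | responding | r | Q | lambda | df | power |
|---|---|---|---|---|---|---|
| 1 | 1 | - | 1 | 9.99 | 2, 71 | 79.7% |
| 3 | 1 | 0 | 1 | 9.99 | 6, 67 | 59.6% |
| 10 | 1 | 0 | 1 | 9.99 | 20, 53 | 30.3% |
| 24 | 1 | 0 | 1 | 9.99 | 48, 25 | 12.6% |
| 26 | 1 | 0 | 1 | 9.99 | 52, 21 | 11.3% |
| 30 | 1 | 0 | 1 | 9.99 | 60, 13 | 8.9% |
| 3 | 3 | 0.3 | 1.875 | 18.73 | 6, 67 | 89.3% |
| 3 | 3 | 0.7 | 1.25 | 12.49 | 6, 67 | 71.1% |
| 3 | 1 | 0.7 | 2.361 | 23.59 | 6, 67 | 95.6% |
| 26 | 26 | 0.5 | 1.926 | 19.24 | 52, 21 | 19.4% |
| 26 | 13 | 0.3 | 10.05 | 100.4 | 52, 21 | 90.9% |
| 26 | 26 | 0 | 26 | 259.74 | 52, 21 | >99% |

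The averaged form of the multivariate test (simulated, hypothesis df 2, error df 144) loses less when only one outcome responds and r = 0: 62% at p = 3, 38% at p = 10, 21% at p = 26 and 18% at p = 30. If all 88 recruits were retained, the doubly multivariate figures under the same condition would be 69% at p = 3, 17% at p = 24 and 13% at p = 30.

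**Step 3: read the results together.** The same N and the same effect on gait speed give anything from 9% to above 99%, according to quantities that the article does not state. Only p = 1 returns essentially the printed figure without a further assumption.

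**The case against.** The strongest reply is that the article does not put all Table 1 outcomes into one model. It ranks outcomes as primary, secondary and tertiary, and Mauchly's test belongs to the univariate repeated-measures F. If gait speed is analysed alone, the multivariate test has 79.7% power and nothing material is lost. A separate analysis plan may also list the models. Part of this stands: a missing list of models is not a defect here, and the all-outcome MANOVA is only one reading. But a single-outcome reading leaves the multicollinearity check without meaning, and the article states an 80% for one kind of test while writing another.

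A reader might go further and infer that the trial really has only some 10-40% power and would usually miss the effect it was sized for. The documents do not support that. The low figures need many outcomes, an effect in gait speed alone, and no correlation between outcomes. That last pair is hard to believe when Table 1 also holds cadence, step length and maximum speed, since speed is cadence times step length. With 13 of 26 outcomes responding at r = 0.3, power is 91%. For the same reason one cannot say that the 80% holds only for a small outcome set.

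Nor does it stand that the test could not be computed. That needs 37 or more dependent variables (2 x 37 = 74, above the 72 error degrees of freedom), reached for example by entering forces and gait phases in both units, whereas section 2.4 standardises the forces by weight. No passage says that a null MANOVA would be read as proof of no benefit; the Abstract ties the decision to the size of effect achieved and the comparison with control.

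**Conclusion.** The point holds as a mismatch between sections 2.2.4 and 2.4. There is no arithmetic error: 74 is right for a one-outcome Group x Time interaction at rho = 0.5 with sphericity. That 80% cannot be carried over to the MANOVA as written, and the primary outcome has no named test to which it could attach.

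The loss of power cannot be stated as one number. If only gait speed responds and outcomes are uncorrelated, the doubly multivariate test has about 60% with the three primary and secondary outcomes and 9-13% with 24-30. If several outcomes respond, or their correlations are favourable, it can exceed 80%. All these figures rest on assumed values of rho, r, p and the number of responding outcomes.

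**What to change.** In section 2.4, name a univariate analysis of gait speed (mixed model or repeated-measures ANOVA, with the group contrast at t1) as the primary test, and say that it does not depend on a significant MANOVA. Keep any MANOVA as secondary, on a small named set such as the three speed outcomes.

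In section 2.2.4, state that 74 participants at 80% power refers to the gait-speed Group x Time interaction, print the assumed correlation and sphericity, and do not attach the 80% to the MANOVA. The t1 contrast should not borrow the figure without its own calculation either, because its power depends on how the effect is spread over t1 and t2.

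The cost is wording in two sections and no extra participants. The drawback is that any multivariate test that is kept carries no 80% power claim.

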**Methods:**

The GAITimagery is designed as a double-blind, randomized control trial, including a convenience sample in 2 parallel groups (1:1) with two interventions of 2 sessions per week during 6-week and 8-week follow-up. The initial recruitment will be 88 participants with idiopathic PD and unimpaired cognition state, who will be randomly divided into two groups: GAITimagery (GiG) or the active control Gait group (GaG). Both will perform the same gait exercises but only GiG will include MI training. Gait speed is the primary outcome, while Maximum gait speed (m/s) and Gait speed variability are the secondary results. The tertiary outcomes are related to Quality of life, Daily life activities, Freezing of gait, Balance, Mobility, and Gait performance measures to psychometrics and biomechanics instruments. All results will be measured at baseline (t0), post-training (t1), and follow-up assessment (t2) 8 weeks after finished physiotherapy programs.

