### Study design

2.1

The GAITimagery is designed as a double-blind, randomized control trial with 6 weeks of intervention (two sessions weekly) and 8 weeks of follow-up. The study considered a convenience sample (specifically, modal instance sampling) in two parallel groups (1:1), and an additional matched-healthy group (Figure 1). This protocol used the Standard Protocol Items for Randomized Trials (SPIRIT) guidelines (28) (Supplementary material 1) and the Consolidated Standards of Reporting Trials statement for randomized controlled trials (29) as a guide to be designed. The Human Research Ethics Committee of the Experimental Research Ethics Commission of the University of Valencia approved all the procedures with the number 1557673 (Supplementary material 2) on 11 February 2021. Then it was registered on ClinicalTrials.gov with the number NCT04788693.

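### Section 2.2.4: 88 recruits allow for about 16% drop-out from a requirement of 74, not the stated 20% (minor arithmetic error)

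*Protocol article*

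**What the plan says.** Section 2.2.4 (Sample size and recruitment) reports a G*Power 3.1 calculation. On the effect size it says "the estimation was settled with a small expected size effect of *F* = 0.15 (60", and on the error rates and design "A power of 80% and a type I statistical error of 5% were considered in a mixed factorial design (2 groups and 3 times assessments". The result is given as "which resulted in 74 participants as the total sample size". The drop-out allowance follows directly: "Considering 20% of drop-outs, the recruitment will be 44 people per group". The abstract repeats the total: "The initial recruitment will be 88 participants with idiopathic PD and unimpaired cognition state". Section 2.1 sets equal allocation, "in two parallel groups (1:1". The article gives no other loss rate and no other reason for 88.

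**The concern.** A drop-out allowance should make the number recruited, less the expected losses, equal the number required. At the plan's own 20% rate, 88 recruits do not yield 74 completers. Adding 20% of the target is a common slip, because the losses come out of the larger recruited number.

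The figure also has a practical role. Section 2.2.4 keeps recruitment open until the calculated number is reached, within a two-year limit, so too low a figure closes recruitment slightly early. At stake are a few completers and a small amount of power for the comparison of gait training with and without motor imagery.

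**Working it through.** **Inputs from the article.** Effect size f = 0.15, α = 0.05, target power 80%, k = 2 groups, m = 3 assessments, required total 74, drop-out 20%, recruitment 44 per group (section 2.2.4); total 88 (abstract); 1:1 allocation (section 2.1).

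**Inputs assumed.** Correlation among repeated measures ρ = 0.5 and no departure from sphericity (ε = 1). The article states neither.

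**Step 1: reproduce the 74.** For the group-by-time interaction, use the noncentral F distribution with

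- λ = f² × N × m / (1 − ρ)
- df1 = (k − 1)(m − 1) = 2
- df2 = (N − k)(m − 1)

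At N = 74, λ = 0.0225 × 74 × 3 / 0.5 = 9.99 and df2 = 144, which gives power of 80.6%. At N = 72 power is 79.5%. So 74 is the smallest balanced total that reaches 80%, and the plan's figure reproduces. Other correlations do not give it: ρ = 0.4 needs 88 before any drop-out, and ρ = 0.6 needs 60.

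**Step 2: the drop-out allowance.**

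- Number to recruit so that 74 remain: 74 / (1 − 0.20) = 92.5, so 93, or 94 (47 per group) when balanced.
- Multiplying instead: 74 × 1.2 = 88.8, or per group 37 × 1.2 = 44.4. Cut to whole people per group, either gives the stated 44.

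**Step 3: what 88 delivers.**

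- Completers after 20% loss: 88 × 0.8 = 70.4, about 35 per group against 37 required.
- Losses that 88 can absorb: 88 − 74 = 14, and 14/88 = 15.9%.

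**Step 4: power at that number.**

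| Recruited | Completers at 20% loss | λ | df2 | Power |
|---|---|---|---|---|
| 88 | 70 | 0.0225 × 70 × 3 / 0.5 = 9.45 | 136 | 78.2% |
| 94 | 75 | 0.0225 × 75 × 3 / 0.5 = 10.125 | 146 | 81.2% |

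The result depends on sphericity. With ε = 0.9 the power is 77.5% at N = 74 and 75.0% at N = 70, but 80 participants would then be needed, so that setting does not reproduce the plan's 74. The multivariate form of the test gives 79.7% at 74 and 77.2% at 70. In each case the step from 74 to 70 costs about 2.5 percentage points.

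**Step 5: the batches in section 2.3.** Randomisation is done in recruitment groups of 12, six times, with a last group of 14. If the last group is the sixth, the total is 5 × 12 + 14 = 74. If it comes in addition, the total is 6 × 12 + 14 = 86. Neither is 88.

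**The case against.** **The effect is too small to matter.** This largely stands. Power is 1.8 points below 80%, and f = 0.15 was adopted because earlier trials had shown no group difference, so uncertainty about the effect size outweighs four completers. That makes the error minor, but it does not make the recruitment figure right.

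**Drop-outs may still contribute data.** The primary time point is post-training, eight weeks before the follow-up visit, so some who leave may have a primary outcome. Section 2.4 also invokes intention-to-treat principles if adherence problems occur. This is partial relief only. The planned mixed MANOVA over three assessments uses complete cases unless missing values are handled, and the allowance itself treats drop-outs as lost.

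**The mechanism is inferred.** This stands. The article does not show how 44 was reached; multiplication by 1.2 fits the figure but is not documented.

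**Two stronger readings are tempting.** A reader might infer that the stated 80% power is false. The article does not support that: it attaches 80% to 74 participants, which reproduces, and it claims no power after drop-out. A reader might also infer from section 2.3 that only 74 will be randomised, so that 20% loss would leave about 59 and power of about 70%. The abstract and section 2.2.4 both set recruitment at 88, and the batch wording has two readings. It therefore shows only that the sections need reconciling.

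**Conclusion.** The point holds as a minor arithmetic error. The figures 74, 20% and 44 per group are mutually inconsistent, and this needs no assumption beyond the article's own numbers and its treatment of drop-outs as lost. The shortfall is about 4 completers, or 5 to 6 recruits (93, or 94 balanced, against 88).

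The power of about 78% is conditional. It assumes ρ = 0.5, sphericity, 88 people randomised, and no contribution from those who drop out. The first two are unstated but well supported, because they return exactly 74. The error does not threaten the trial's conclusions. The mismatch with the batches in section 2.3 is a separate inconsistency, and the estimate here does not depend on how it is resolved provided that 88 are randomised.

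**What to change.** Correct the one sentence in section 2.2.4 in one of these ways:

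- Keep 88 and state that it allows for about 16% drop-out (14 people).
- Keep 88 and 20%, and state that about 70 would complete, with power of about 78%. Give the assumed correlation and sphericity alongside.
- If both 20% and 80% are to be kept, recruit 94 (47 per group) and change the abstract total to match.

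The first two cost a sentence and a slightly less favourable figure. The third costs six more participants.

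Separately, rewrite the batch description in section 2.3 so that its sizes add up to the recruitment total finally stated. That is a wording change and should be settled before recruitment, which section 2.2.1 expects to begin in September 2025.
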